##### EQ-5D [59]

The EuroQol or EQ-5D is a standardized questionnaire for use as a measure of health outcome. The EQ-5D-3 L (five dimensions, three levels) used in this study consists of the descriptive system and the EQ-5D visual analogue scale (EQ-5D VAS). The descriptive system comprises five dimensions: mobility, self-care, usual activities, pain or discomfort and anxiety or depression. Each dimension has three levels, no problems, some problems and extreme problems, and the respondent is asked to tick the box against the most appropriate statement in each of the five dimensions. The VAS records the respondent’s self-rated health on a vertical, visual analogue scale (0 to 100) with endpoints representing the worst and best imaginable health states. Both the self-completed parent- and proxy-parent-reported child measures are used in this trial. This is a generic measure, applicable to a wide range of health conditions and can be used in the clinical and economic evaluation of health care. The parent-completed measure is widely used and has shown moderate levels of validity. The parent-proxy measure has not been sufficiently validated, particularly with younger children. However, Matza and colleagues [74] have looked at the parent-proxy ratings of children with ADHD in the USA and UK and reported that it was able to detect impairment in these children. The index and the VAS also showed significant correlations with ADHD symptoms using DSM-IV criteria for ADHD. Matza et al. concluded that parent-proxy ratings are feasible and valid for use as part of an overall health outcomes assessment in clinical studies of childhood ADHD [74].

#### Mediators

The following measures allow investigation of the possible role of positive and constructive parenting and scaffolding, improved maternal mental health and improved inhibition with greater delay tolerance by the child in mediating the impact and effectiveness of the parenting intervention.

##### Expressed emotion (EE): five-minute preschool speech sample (FMSS: [60])

The parent is asked to speak for exactly 5 minutes about his or her child, his or her feelings and thoughts about the child, and how they get along together. The parent is to use his or her own words without any interruptions from the interviewer. The parent’s response is taped. Parental EE is rated on the initial statement, warmth, emotional overinvolvement, relationship, positive and critical comments. A coding manual is used for the FMSS. An overall score can be given for the level of EE with a high level indicating a negative influence. The measure has shown acceptable code-recode and interrater reliability and adequate test-retest reliability. It also demonstrated to have acceptable validity, being associated with less affection and greater maternal direction during play interaction, and discriminating between the parents of preschool children with symptoms of ADHD and those without such symptoms [60]. Training of research fellows in the administration and scoring of the FMSS will be overseen by the author of this measure (DD).

##### Global impressions of parent–child interactions - revised (GIPCI-R: [61,62])

This measure involves the direct observation of mother-child interactions while completing three tasks, each of 5 minutes’ duration: ‘jigsaw’, ‘free play’ and ‘tidy-up’. The 15 minutes of parent–child interaction are videotaped and coded at a later time using the GIPCI coding manual. Child items rated are: respect, destruction, disruptive, noncompliance, social skills, valence and disconnection. Parent items rated are valence, responsiveness, warmth, praise, enjoyment, scaffolding, effectiveness, aggression and criticism or punishment. The measure generates summary global ratings (1 to 5) for both parent and child behaviours with a higher score indicating a more positive outcome. Thompson et al. [26] found adequate interrater reliability for child scores across all item codes (0.62; range 0.48 to 0.77) and for parent scores (0.64; range 0.48 to 0.79). There was also good internal consistency for child and parent scales (0.84; 0.87). Test-retest reliability was adequate for the parent measure (*r* = 0.50) but low for the child measure (*r* = 0.20). Training in administration and scoring will be carried out by the clinical lead in the trial (MT).

##### Delay of gratification: cookie delay task [63]

This task involves placing an edible treat under one of three upturned transparent cups and asking the child to wait for a signal before retrieving the treat. Eight trials are given in a pseudorandom order with delays of between 5 and 30 seconds. The scoring is 0 = not inhibited, 1 = partially inhibited and 2 = fully inhibited, giving a possible range of scores 0 to 16. The task has been shown to be reliable and to discriminate between hard-to-manage preschoolers and their peers [75].

##### General health questionnaire (GHQ: [64])

The parent-completed GHQ was developed as a screening instrument for use in primary care settings to identify those likely to have or be at risk of developing psychiatric disorders. It is a measure of common mental health problems, such as depression, anxiety, somatic symptoms and social withdrawal. This trial employs the 12-item version of the GHQ, which has been shown to be consistent and reliable across time. Items are scored from 0 to 3, with a total score ranging from 0 to 36, where a lower score indicates health and a higher score indicates illness. This measure is widely used and has shown adequate reliability and validity over a number of studies.

#### Moderators

The possible moderating role of high-risk factors, including the presence of maternal ADHD symptoms, and other indicators of poor outcome and long-term high burden will be investigated. Measures will also be used to monitor process and treatment fidelity across both parenting programmes.

##### Current symptoms scale (CSS: [67]

The CSS is an 18-item questionnaire designed to assess ADHD symptoms in adults and is based on the DSM-IV definition of symptoms of ADHD. The CSS self-report scale requires adults to rate the frequency of their own symptoms over the previous 6 months on a 4-point scale ranging from 0 (rarely) to 3 (very often). A score of nine symptoms or more experienced as ‘often’ or ‘very often’ is used as the standard cut-off to identify adults at risk of clinical problems of ADHD. The scale has been shown to be correlated with spousal, parental and cohabiting partner ratings of symptoms. It comes with a manual for hand scoring, has age- and sex-specific norms and has good psychometric properties, including acceptable levels of internal consistency and excellent test-retest reliability.

##### Preschool ADHD risk index (PARI)

The aim of one of the projects in the 5-year Programme for Detection and Early Intervention for ADHD is to develop the PARI, a way to identify preschool children with ADHD most at risk of poor outcome and high burden. This is based on a prospective follow-up of a large sample of individuals who were identified as having symptoms of ADHD at a preschool age in the 1990s but are now entering late adolescence or early adult life. The risk index is derived from a statistical process involving (i) identification of those children with high levels of ADHD symptoms at 3 years who fall into high- and low-burden groups and (ii) the use of logistic regression to model child, parental and socioeconomic predictors of poor outcome and high burden in the sample of children. Ten parameters will be included in the model: initial ADHD symptom levels; socio-emotional problems; temperament; language delay; developmental delay; maternal mental health; maternal age; parental marital status; perinatal risk and social class. This information will be obtained from a number of sources, including birth and patient records, a demographic questionnaire and the current trial measures (for example, maternal mental health). The temperament measures will be taken using the EASI scale, a 10-item scale measuring emotionality (five items) and shyness (five items), giving a score out of 5 for each subscale [76]. The index so developed and used in the current study will include the significant predictors of high burden weighted in relation to the strength of their contribution to the regression model. The final form taken by the index which will be used will be based on data collected from the ongoing PARI study and is not currently known at present.

##### Leader Observation Tool (LOT: [53])

Process fidelity will be measured using a modified version of the LOT after treatment is finished. This revised version is adapted from the LOT tool used to successfully monitor the fidelity of the IY, which is delivered to parents in a group format. Random sessions from the videotaped IY and adapted-NFPP therapy sessions will be observed and coded by an independent observer, who will score adherence to content week by week as well as the process by which the programme is delivered. The LOT has high internal reliability and good code-recode and interrater reliability. Evidence of concurrent validity has also been obtained.

##### Working alliance inventory, short form: parent and therapist versions (WAI-S: [54])

The WAI-S is a 12-item self-report measure of working alliance. The working alliance is an important part of the process of therapy, and looks at the alliance of task, goals and relationship of therapist with parent and vice versa. Most studies suggest that this alliance is usually forged within 2 to 4 weeks of the beginning of therapy. Two versions of the WAI-S are available: a client version and a therapist version. In this trial, both versions will be completed by the parent and therapist in weeks 6 and 12 of the parenting programme with each form being treated as confidential and delivered to the research office in a sealed envelope by the therapist. The authors of this measure found a correlation with outcome. The WAI-S has three subscales: goals, tasks and bond. Each subscale is scored on a 7-point Likert-type scale ranging from 1 (never) to 7 (always) and has four nonoverlapping items. Subscale scores can range from 4 to 28, to produce a total score of 12 to 84 with higher scores reflecting more positive ratings of working alliance. Internal consistency estimates of the three subscale scores, based on an initial validation sample of 124 pairs of parents and their therapists, ranged from 0.90 to 0.92 (client version) and 0.83 to 0.91. Internal consistency estimates of the total scores were 0.98 (parent version) and 0.95 (therapist version [54].

##### Family Strain Index (FSI: [55])

Impact of treatment on the family will be measured using the FSI questionnaire at the start and end of the parenting programme. This six-item questionnaire is designed to measure two primary aspects of stress and demand on parents and families, specifically, the ‘emotional’, and ‘restrictiveness’ experiences of living with a child with ADHD. Parents will be asked to rate the frequency of occurrence of each of six items over the past 4 weeks on a 5-point scale scored 0 (never) to 4 (always) with a total score in the range 0 to 24. This measure will be used at baseline and at the end of therapy.

The measure has been shown to have excellent internal consistency across the six items (Cronbach’s α = 0.83 to 0.87) and for the full scale (Cronbach’s α = 0.87).

### Statistical analysis

The main analyses will be performed using the intention-to-treat population. All results will be reported according to the CONSORT statement for nonpharmacological interventions [66]. The primary endpoint for the comparison between adapted-NFPP and IY will be the average ADHD score on items 1 to 18 of the SNAP-IV-P at post-treatment. The primary analysis of this endpoint will adjust for baseline SNAP-IV-P scores using a mixed-effect regression model [77] with treatment arm and time (pre- and post-treatment) as the fixed effects and therapist as a random effect. Subject to approval, this analysis will also include trial centre and recruitment tranche as randomization stratification factors. These models are especially valuable when used with longitudinal and trial data derived from parallel arms. A similar secondary analysis comparing adapted-NFPP and IY will be carried out 6 months after treatment. Secondary outcome measures, including the Child’s Solo Play Index, ECBI (Parent), ADHD SNAP-IV-T and SNAP-IV-T, together with SNAP-IV-P ODD scores, will be analyzed in the same way as SNAP-IV-P ADHD.

Subject to approval, a per-protocol analysis will also be performed. The parent will be considered to have completed the parenting programme if he or she had completed at least 8 of the 12 programme sessions. In the case of the IY programme, this will be either by attending the group or by receiving individual home-based sessions for any missed sessions.

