#### Therapist effects

Four or more therapists (depending on numbers recruited) will work in each of the three study centres with two therapists working on each intervention. The mixed effects regression models will include therapist as random effects within these models, allowing for the extent to which treatment effects differ between therapists and also accounting for the way in which participants are nested by therapist. Even when the difference between treatment effects can be assumed to be identical for all therapists, the mixed model can improve the precision of the treatment estimates by taking appropriate account of the different therapists in the analysis.

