#### Moderator analysis

The presence of parental ADHD will be assessed using the CSS [65]. This score will be collected at baseline and an interaction term (CSS * treatment group) will be included in the mixed-effect regression models to determine whether parent training might be less beneficial for children whose parents demonstrate symptoms of ADHD. The interaction term will be considered significant for *P* < 0.05.

Risk of long-term burden as assessed by the PARI will be included in the mixed-effect regression models to determine whether this measure moderates the effect of treatment on primary and secondary outcomes.

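### The terms listed for the primary model do not estimate the post-treatment difference named as the endpoint; taken as listed, the arm coefficient is about half of it

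*Protocol article*

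**What the plan says.** All of the following is from the Protocol article.

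- **Endpoint (Statistical analysis).** For adapted-NFPP versus IY, the primary endpoint "will be the average ADHD score on items 1 to 18 of the SNAP-IV-P at post-treatment". This is one score per child at one time point.
- **Baseline (Statistical analysis).** "The primary analysis of this endpoint will adjust for baseline SNAP-IV-P scores using a mixed-effect regression model".
- **Model terms (Statistical analysis).** The model is specified "with treatment arm and time (pre- and post-treatment) as the fixed effects and therapist as a random effect".
- **Further terms (Statistical analysis).** "Subject to approval, this analysis will also include trial centre and recruitment tranche as randomization stratification factors".
- **Random effects (Therapist effects).** The therapist effect is described as "accounting for the way in which participants are nested by therapist". Two scores from the same child are not mentioned.
- **Other outcomes (Statistical analysis).** The secondary outcomes are to be analysed in the same way as the primary one. The comparison of the two programmes six months after treatment is to use a similar analysis.

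**The concern.** Making pre- and post-treatment two levels of a time factor puts the baseline score into the outcome. An arm effect in such a model, with no arm-by-time term, is an effect assumed equal at both times. T1 measures are taken before randomisation (Informed consent), so the expected arm difference at T1 is zero. The arm coefficient then mixes that zero with the difference the trial wants to know.

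Two further features follow from the same list. With therapist as the only random effect, a child's two scores are treated as independent, apart from any shared therapist. And if adjusting for baseline means a covariate, baseline serves both as an outcome row and as a predictor.

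At stake is the headline mean difference with its confidence interval, and the same quantity for every secondary outcome. The sample size is built on a post-treatment difference of 0.28 (0.4 SD), and the listed model would not report on that scale.

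**Working it through.** **Inputs.** From Sample size: difference 0.28, SD (s) 0.7, two-sided 5%, 80% power, design effect 1.28, 10% drop-out, n = 127 analysed per active arm. The pre-post correlation r of SNAP-IV-P is not given, so 0.3, 0.5 and 0.7 are assumed. Both time points are given the same SD.

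**The plan's own figure.** n per arm = 2 × (1.96 + 0.842)² × 0.7² / 0.28² = 98.1, rounded up to 99. Then 99 × 1.28 = 126.7, and 126.7 / 0.9 = 140.8, so 141 per arm. The stated 141 is reproduced, and it rests on a difference of 0.28 at T2.

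**Reading A: baseline enters only as the pre level of time.** Write d_pre and d_post for the arm differences at T1 and T2.

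- Arm coefficient = (d_pre + d_post)/2, with expectation (0 + 0.28)/2 = 0.14.
- Standard error the model reports, treating rows as independent: 0.7 × √(2/254) = 0.062.
- True standard error: 0.7 × √((1 + r)/127) = 0.071, 0.076, 0.081 for r = 0.3, 0.5, 0.7.
- Type I error = 2 × [1 − Φ(1.96/√(1 + r))] = 8.6%, 11.0%, 13.3%.
- Power = Φ((0.14 − 1.96 × 0.062)/true SE) ≈ 60%, 59%, 59%.

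**Reading B: baseline is also a covariate.** Let b be the slope of T2 on T1 (b = r here).

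- The pooled baseline slope over the two rows is (1 + b)/2.
- Arm coefficient = (d_pre + d_post)/2 − d_pre(1 + b)/2 = (d_post − b × d_pre)/2. This is exactly half the ANCOVA estimate, for any r.
- True standard error = half the ANCOVA standard error = ½ × 0.7 × √(2(1 − r²)/127) = 0.042, 0.038, 0.031.
- Model standard error under no effect = √(s²(1 − r)(3 + r)/4 / 127) = 0.047, 0.041, 0.033. It is too large, so type I error is 2.7%, 3.4%, 4.1%.
- With a true 0.28, the omitted interaction adds 0.07² = 0.0049 to the residual variance, giving model standard errors of 0.048, 0.042, 0.033. Power = Φ((0.14 − 1.96 × SE)/true SE) ≈ 87%, 94%, 99%. ANCOVA gives 92%, 96%, 99%.
- The 95% interval is centred on 0.14 and covers the true 0.28 in about 13%, 6% and 1% of trials.

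**Simulation** (3,000 replicates per setting, no clustering). The mean arm coefficient was 0.14 under both readings, against 0.28 for ANCOVA. Under reading B, twice the coefficient equalled the ANCOVA estimate to machine precision in every replicate. Coverage of 0.28 ran from about 1% to 15% across repeated runs, against about 95% for ANCOVA.

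**With a therapist random intercept** (60 runs; 6 therapists per arm, therapist ICC 0.05 and r = 0.5, all assumed). The arm coefficient was 0.152 with the covariate and 0.146 without. ANCOVA gave 0.303 and the arm-by-time term 0.308. The halving remains.

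**Clustering and the ANCOVA power.** The 92% at r = 0.3 ignores the design effect. At 127/1.28 = 99.2 per arm it is Φ(0.28/0.095 − 1.96) ≈ 84%.

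**The case against.** The strongest reply is that the document names factors without saying that they enter as main effects only. It does not exclude a participant effect, and it does not say that the arm coefficient is what will be reported. Coding of interactions and within-child covariance is often left to a full protocol or analysis plan, neither of which is shown. One might answer that the article spells out interactions where it wants them, as in "an interaction term (CSS * treatment group) will be included in the mixed-effect regression models". That answer is weak: in the same section the risk index is to be tested as a moderator with no interaction written out, so the article does leave some necessary interactions implicit. The stated endpoint also tells an analyst what to aim for.

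This limits the point but does not remove it. The article does more than stay silent: it writes out the primary model, and the terms it gives do not deliver the endpoint named in the preceding sentence.

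Three stronger readings are tempting and not supported:

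- **That the trial will report half the effect.** This would need the listed terms to be the final model and the arm coefficient to be the reported effect. The document fixes neither.
- **That the plan inflates type I error and loses much power.** This holds only if baseline is not a covariate. With the covariate, which is the natural sense of adjusting for baseline, the test is slightly conservative and loses little power.
- **That the conditional wording on centre and tranche is part of the same fault.** It is a separate matter with no bearing on the halving, and it may only record a pending approval.

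**Conclusion.** The point holds as a mismatch between a stated endpoint and a stated model. Taken as listed, the arm coefficient estimates about half the T2 difference: 0.14 (0.2 SD) when the truth is 0.28 (0.4 SD). In expectation this depends neither on the unknown pre-post correlation nor on whether baseline is also a covariate. The consequences for the test do depend on that choice:

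- **Baseline as covariate:** the estimate is halved and its interval rarely covers the true value, but the test is nearly intact.
- **Baseline only as the pre level of time:** type I error is also about 9% to 13% and power about 60%.

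The error rates, power and coverage assume correlations of 0.3 to 0.7, 127 per arm and no clustering. The sample size itself needs no change. Because this is the primary analysis, the wording should be settled before it is run.

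**What to change.** State the primary model in one of two forms.

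1. **Post-treatment regression.** Outcome: mean of SNAP-IV-P items 1 to 18 at T2. Fixed effects: arm, T1 score, centre and tranche. Keep the random effect for therapist (or IY group), which the Therapist effects section calls for, and drop the time factor. The treatment effect is the adjusted arm difference at T2.
2. **Pre/post model.** Keep T1 in the outcome and not as a covariate. Give the arms a common baseline mean, and include arm-by-time, a participant random intercept and the therapist random effect. Report the arm contrast at T2, and at T3 for adapted-NFPP versus IY.

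Carry the same form over to the secondary outcomes. If a statistical analysis plan already contains these terms, align the protocol wording with it. The cost is wording only: every variable is already collected, and neither the sample size nor the visit schedule changes.

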### Sample size

The trial is powered for two comparisons of interest.

Primary question: adapted-NFPP versus Incredible Years (Arm A vs Arm B).

Is adapted-NFPP superior to IY in terms of reductions in parent-rated ADHD symptoms? Assuming a conservative estimate of effect size difference of 0.4 standard deviation between adapted-NFPP and IY, an intraclass correlation of 0.08 for parents treated in the same IY groups and a drop-out rate of 10% (considerably higher than in the original trials) it is estimated that 141 individuals will be needed per treatment arm to provide sufficient power to test the hypothesis that the adapted-NFPP is superior to IY in terms of reduction in ADHD symptoms (total *N* = 282). This equates to a difference of mean 0.28 and standard deviation 0.7 on the SNAP-IV-P ADHD rating scale (the primary outcome) using a 5% two-tailed test of significance and 80% power. A design effect of 1.28 has been calculated from the formula:

$$1+\left(m-1\right)p$$

in the CONSORT (Consolidated Standards of Reporting Trials) statement for nonpharmacological interventions [66].

Secondary question: adapted-NFPP versus treatment as usual (Arm A vs Arm C).

Is the adapted-NFPP superior to TAU in terms of reductions in parent-rated ADHD symptoms? Again assuming a conservative estimate of effect size difference between adapted-NFPP vs TAU, a group of 141 adapted-NFPP and 47 TAU will give 81% power to detect an effect size of 0.5 on the SNAP-IV-P ADHD score (equating to a difference of mean 0.35 and standard deviation 0.7) with 5% two-tailed significance. No intraclass correlation has been applied for this calculation, as both adapted-NFPP and TAU will be delivered individually.

On this basis, each of the three centres will recruit approximately 110 families with a preschool-aged child (age 2 years 9 months to 4 years 6 months) with high levels of ADHD symptoms (total *n* = 329) into the trial. Families will be randomized with intention to treat to either (i) adapted-NFPP as an individually delivered, home-based parenting programme (*n* =141, leaving 127 for final analysis with 10% drop-out); (ii) IY delivered in groups of eight (*n* = 141, leaving 127 for final analysis with 10% drop-out); or (iii) TAU (*n* = 47, leaving 42 for the final analysis with 10% drop-out).

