### Recruitment

The plan for recruitment takes into account that (a) two research fellows will be available at each centre to conduct screening and the diagnostic interview, recruit participants to the study and complete T1 to T3 visits for each tranche and (b) two pairs of therapists will be employed at each centre to cover the two parenting programmes. Given a target recruitment of *n* = 329 participants (110 participants per centre) and factoring in school holiday periods, it is estimated that five or six parenting programme tranches will be needed, with 18 to 22 parents enlisted per tranche across centres. An allocation ratio of 3:3:1 will mean that approximately eight parents will be allocated to each pair of therapists. Two NFPP therapists will each work on a one-to-one basis with four parents over the 12-week period of the programme and two IY therapists or leaders will conduct a group-based programme in a local hall with eight parents, whose partners may also attend the group.

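### The primary comparison is sized for clustering by IY group but modelled with therapist only; the cost is small if the post-treatment score is analysed and about 8–10% type I error if pre and post rows share one therapist intercept

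*Protocol article*

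**What the plan says.** All references are to the protocol article.

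- **Sample size.** The primary comparison assumes "an intraclass correlation of 0.08 for parents treated in the same IY groups", with "IY delivered in groups of eight", and is sized "using a 5% two-tailed test of significance and 80% power".
- **Recruitment.** For each centre and tranche, "two IY therapists or leaders will conduct a group-based programme in a local hall with eight parents". Five or six tranches are expected, with one pair of therapists per programme at each centre.
- **Statistical analysis.** The endpoint is the post-treatment SNAP-IV-P ADHD score. The model is to adjust for baseline and to have "treatment arm and time (pre- and post-treatment) as the fixed effects and therapist as a random effect". Centre and tranche are added only if approved. Secondary outcomes use the same model, and the 6-month comparison a similar one.
- **Therapist effects.** The therapist random effects are described as "accounting for the way in which participants are nested by therapist".

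No random effect for IY group is named in any of these sections.

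**The concern.** The clustering that raised the sample size is not the clustering in the model. Three features make this more than a difference of wording.

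1. Each IY group has two leaders, so every IY family belongs to both. Nesting in single therapists does not describe that arm, and the text does not say how co-led groups are coded.
2. One pair covers five or six groups. Correlation specific to a group is therefore not the same thing as correlation specific to a pair. Centre and tranche main effects cannot represent it either, because a group is one centre-by-tranche cell within the IY arm only.
3. The text both adjusts for baseline and lists time (pre and post) as a fixed effect. If the baseline score is a row of the outcome, a therapist intercept common to both rows drops out of the change from pre to post. Correlation that arises during group treatment then has no term to carry it.

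At stake is the standard error of the primary comparison and, because the model is reused, those of the secondary and 6-month comparisons.

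**Working it through.** **1. The plan's own sample size.** "This equates to a difference of mean 0.28 and standard deviation 0.7", so the effect is 0.28/0.7 = 0.4 SD.
- Unclustered: n = 2(1.96 + 0.842)²/0.4² = 98.1, so 99 per arm.
- "A design effect of 1.28 has been calculated from the formula" 1 + (m − 1)ρ. With m = 8 and ρ = 0.08, the IY arm has 1 + 7 × 0.08 = 1.56. The average with 1.00 for the individually treated arm is 1.28, which matches.
- 99 × 1.28 = 126.7, so 127. Then 127/0.9 = 141.1, which matches the stated 141.

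Group clustering therefore accounts for the step from 99 to 127 analysed per arm.

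**2. Units in the IY arm.** 141/8 = 17.6 groups, or 3 centres × 6 tranches = 18. With one stable pair per centre there are 3 leader pairs. About 127/18 = 7 families per group are analysed.

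**3. No clustering term at all (benchmark).** With 7 per group the IY arm has 1 + 6 × 0.08 = 1.48, and the two-arm average is 1.24. Type I error is 2[1 − Φ(1.96/√1.24)] = 7.8%. With 8 per group (1.28) it is 8.3%.

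**4. Post-treatment score, random therapist.** REML simulation with 18 IY groups of 7, 126 per arm, group ICC 0.08, no true effect, Wald test at 1.96 and 2,000 runs per scenario. Four codings were used: IY therapist as pair or as single leader, with and without centre and tranche. The therapist ICC of 0.03 is an assumption and is not in the documents.

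| Random effects | Type I error, no therapist variance | Type I error, therapist ICC 0.03 |
|---|---|---|
| None | 7.4–8.3% | 17.6–19.4% |
| Therapist only (as written) | 5.1–6.2% | 8.7–12.8% |
| IY group only | 5.1–5.7% | 13.2–14.4% |
| Therapist and IY group | 3.7–4.5% | 7.3–10.1% |

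With pair coding and no strata, the mean model SE under therapist-only is 0.144 SD against an empirical 0.141. Groups lie within pairs and pairs within arm, so the therapist variance picks up most of the group variance that bears on the arm contrast.

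**5. Pre and post rows, common therapist intercept.** Assume an arm-by-time contrast, a participant-level correlation r between rows, unit variance at each time, and group variance 0.08 arising at post-treatment only. The variance of change is 2(1 − r), so the group ICC of the change score is 0.08/[2(1 − r)].
- r = 0.5: ICC 0.08; IY arm 1.48; average 1.24; type I error 7.8%.
- r = 0.7: ICC 0.08/0.6 = 0.133; IY arm 1 + 6 × 0.133 = 1.80; average 1.40; type I error 2[1 − Φ(1.96/√1.40)] = 9.8%.

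Separate simulations gave 7.8–8.2% and 9.7–10.1%. The documents give no pre-post correlation, so r is an assumption.

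**6. Price of carrying both terms.** With therapist and IY group, no true therapist effect and a 0.4 SD difference, simulated power is about 73% with a 1.96 critical value and about 58% with small-sample degrees of freedom. A rough check with the mean SE of 0.1526 from step 4 (pair coding, no strata) gives 0.4/0.1526 = 2.62 and Φ(2.62 − 1.96) = 75%, close to the first figure. For comparison, therapist-only tested on 7 therapist-level degrees of freedom gave about 2% type I error and 65–66% power.

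**The case against.** The strongest reply is that the stated endpoint is the post-treatment score adjusted for baseline, and that on this reading group clustering is largely handled: 5.1–6.2% against 7.4–8.3% with no clustering term. That stands. The Therapist effects subsection also says the random effects let the benefit of treatment vary between therapists. That can be read as a therapist-by-treatment effect that would not cancel. So the 8–10% figure belongs to one literal reading of the model and is not a property of every reading.

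Pairs may also change. The protocol allows four or more therapists per centre and delivery over 2.5 years, and with turnover therapist moves closer to group. This stands as a limit on the three-pair assumption.

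Degrees-of-freedom method and arm-specific variances are ordinary analysis-plan detail, and a condensed article need not give them. That stands too. It does not remove the mismatch, because the article itself names one clustering unit for sizing and another for analysis.

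Three stronger readings are tempting and are not supported:

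- **Group clustering is simply absent, so the primary test must be miscalibrated.** Step 4 shows otherwise for the post-treatment score.
- **The error rate of the therapist-only test is 8%.** About 8% does occur in simulated trials where the therapist variance is estimated as zero (some 46% of them). That is a selected subset; over all trials the rate is close to nominal.
- **Replacing therapist by IY group cures the problem.** A group-only model looks good (4.9% error, 79% power) only when therapists do not differ. At an assumed therapist ICC of 0.03 its type I error is about 10–14%, depending on the simulation set-up, and in step 4 it was worse than therapist-only.

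**Conclusion.** The Sample size section and the Statistical analysis and Therapist effects sections use different clustering units, and the nesting described does not fit co-led IY groups. This needs correction.

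The size depends on a choice the text leaves open. With the post-treatment score and baseline as a covariate, omitting the group term costs about 0–1 percentage point of type I error. With pre and post rows and a therapist intercept common to both, type I error is about 8–10%.

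These figures assume a group ICC of 0.08, 18 groups of 7, one stable leader pair per centre and no separate therapist variance; the second also assumes a pre-post correlation of 0.5–0.7. If therapists do differ, the small number of them matters more than the missing group term. With about three IY pairs, a Wald test is liberal even when both terms are fitted. A group term does not remove that limitation, which belongs to the design.

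**What to change.** Reconcile the Statistical analysis and Therapist effects sections with the Sample size section.

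1. State that the post-treatment SNAP-IV-P score is the outcome and baseline SNAP-IV-P a covariate. If both rows are kept, attach the cluster effects to post-treatment rows only.
2. Keep the therapist random effect and add one for IY group, defined as the centre-by-tranche cell in the IY arm only.
3. Name the leader pair as the therapist unit in the IY arm, and drop the description of IY families as nested in single therapists.
4. Use the same structure for the secondary outcomes and the 6-month comparison.

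The degrees-of-freedom method and any arm-specific variances can be left to the analysis plan.

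The change needs new wording and a few lines of code. Under the planned delivery, group membership follows from centre, tranche and arm. The statistical cost is real: wider intervals, and power at 0.4 SD of about 73% (1.96 critical value) or 58% (small-sample degrees of freedom) against the 80% planned. It should be settled before any unblinded analysis.
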